### Statistical analysis

Analysis of the primary outcome will be carried out on an intention-to-treat basis. For each endpoint, a linear regression will be used to estimate differences in the cluster-level prevalence of the indicator at follow-up. Any indicators unbalanced at baseline will be included as covariates. The Shapiro–Wilk normality test will be used to test for non-normality of the model residuals, and standard non-parametric tests (e.g. Mann–Whitney rank-sum test) will be used in case of non-normality. Effect sizes will be reported with 95% confidence intervals, and results will be considered significant if the *P* value is less than 0.05. Data will be analysed by using STATA.

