### Study design

This is a prospectively registered, three-arm, matched-cluster, randomised controlled trial with single (outcome assessor) masking, intention-to-treat analysis, and 6 months of follow-up (Fig. 1). The study is being implemented in eight sites in Manicaland Province, east Zimbabwe. The study will be implemented site by site. In each study site, a census of all households in the study clusters at baseline will be used to identify 15- to 29-year-old males who are resident within the study site. A detailed individual questionnaire will collect information on primary endpoints and then provider-initiated HIV testing and counselling will be offered. Individuals identified as eligible after this stage will be invited to participate in the intervention.

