**Fig. 1 Fig1:**
[figure not shown]
Study design

In each site, two matched clusters of villages will be created. Clusters will be randomly allocated to the intervention arm or to the control arm. Within the intervention clusters, individuals will be further randomly assigned to receive one of two incentives:
A.An education session offered (30 min) by a circumcised male “role model”, an immediate $5 contribution towards transport costs to the health facility, and a $20 payment (about 2 days of wages), conditional on being circumcised within 6 months, orB.An education session (30 min) offered by a circumcised male “role model”, an immediate $5 contribution towards transport costs, and the following lottery-based financial incentive, conditional on being circumcised within 6 months:
5% (1 in 20) chance of receiving $200 (about 10 times 2 days of wages)95% (19 in 20) chance of receiving $10 (about 1 day’s wage)

In addition, in two of the eight sites, a community-engagement intervention using community conversations (CCs) [14, 15] will be implemented to address social and cultural barriers to taking up VMMC and support the above-mentioned individual-level intervention.

Males in the control clusters will receive no intervention over and above the current national standard of care in Zimbabwe. In the study sites, standard of care, which includes some VMMC demand creation activities, comprises information, education and communication (IEC) materials (including posters featuring people such as famous musicians and soccer players who have taken up VMMC) with additional school and community outreach, social marketing, and market-segmentation approaches being tried in some areas. Population Services International functions as a national-level partner of the Zimbabwe Ministry of Health and Child Care (ZMoHCC) in this programme. Until recently, the programme has focussed largely on youth (10–19 years old).

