
### Inclusion and exclusion criteria

A total of 1740 males will be enrolled on the basis of the following eligibility criteria: (i) if they are between 15 and 29 years of age, (ii) they live in Manicaland province, and (iii) they expect to be resident for the duration of the study. Participants will be excluded if they test HIV-positive at baseline or self-report that they have already been circumcised. To avoid indirect disclosure of the status of HIV-positive individuals, a random sample of 90% of HIV-negative males will be selected to participate in the intervention.

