### Randomisation/masking

Within each study site, two matched clusters of villages will be created on the basis of socio-economic characteristics and factors such as distances to trading centres, major roads and health centres. Control and intervention clusters will be constructed to maximise the distance between them to limit potential contamination. Clusters will be randomly allocated to intervention or control. Males in the intervention clusters will receive the intervention. Males in the control clusters will receive no intervention. Males in both clusters will be followed up for measurement of outcomes at 6 months. For the allocation to one of the two treatment groups, blocked randomisation will be used. Blocks of four will be computer-generated and allocated to one of the two treatment arms in a 1:1 ratio. Study staff will be blinded to a block number and the sequence in a block. The treatments will be assigned by using pre-prepared scratch cards that individuals will be asked to select from a set of cards. These cards will also serve as the VMMC referral documentation at participating clinics. Participants will not be blinded from their allocated trial arm due to cluster level randomisation and the nature of the intervention. Study interventions and measurements will occur in separate locations and time points, thus facilitating the blinding of outcome assessors.

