### Sample size estimates

It is estimated that a sample size of 580 participants per arm will be necessary to detect meaningful minimum effect sizes for the primary endpoint (VMMC uptake). Survey data from the study sites in 2012–13 were used to calculate the mean cluster size, the coefficient of variation in cluster size (0.17 for males), and the intra-cluster correlation coefficient (0.04 using HIV incidence as the outcome). A baseline prevalence estimate for the endpoint indicator (VMMC) was taken to be 30%. It was also assumed that 80% of eligible participants will consent to participate and a further 80% will be followed up at 6 months. The community-led CC intervention will be implemented in the “intervention clusters” in addition to the individual-level VMMC intervention. It will take place in only two cluster pairs, and the analysis will examine the effects of the interventions within these two cluster pairs only so as to allow greater power to detect the effect of the individual-level intervention without CCs. Nevertheless, in the two sites with the combined interventions, the study is powered to detect large impacts on outcome indicators. As a further consequence, there will not be sufficient power to examine the interaction of the effect sizes with and without the addition of the community-level intervention. CCs have been included for exploratory and qualitative reasons, helping us understand the role of social context in shaping uptake of VMMC, for which we consider two sites sufficient.

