## Discussion

This trial will evaluate the impact of an education intervention around HIV risks combined with an up-front compensation and conditional incentives to modify behaviour (uptake of VMMC) delivered through fixed or lottery mechanisms in improving perception of HIV risk and uptake of VMMC amongst males aged 15–29 years. The study will provide reliable and high-quality estimates of the average treatment effects since it is a randomised and prospectively registered study. Outcome assessors will be masked, and the analysis will be based on an intention-to-treat approach. Sample size was calculated to provide adequate statistical power to identify possible differences in the study’s primary outcome. In addition, the 6-month follow-up will allow adequate time for participants to take time off work and present at clinics with referral vouchers for VMMC. The 6-month follow-up period is also not too long to measure adjustment in risk perception. Findings from the study will help determine which type of financial incentive is an effective tool to create demand for VMMC and to adjust HIV risk perceptions.

The present study makes several innovative contributions. It combines social learning to improve HIV risk perception and self-efficacy with behavioural incentives and addresses the fear of pain associated with VMMC and possible present-biased preferences with front-loaded compensations as well as with fixed and lottery-based conditional financial incentives. It is thus evaluating the effectiveness of this combination of different prevention interventions in increasing uptake of VMMC in uncircumcised males aged 15–29 years.

This study has limitations. The study does not test the impact of not providing up-front contributions to transport costs or the impact of the education session alone. Another potential limitation is the possibility of lower-than-expected retention rates as males may move away for employment. Any retention challenges will provide valuable information in planning for future research and intervention implementation. Other limitations of this randomised controlled trial could include recruitment challenges and potential sampling bias. Eligibility, recruitment, enrolment and retention will be closely monitored to overcome such challenges.

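### Fixed versus lottery is randomised within clusters, but the only stated model is a regression on cluster-level prevalence that names no cluster or pair term

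*Protocol article*

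**What the plan says.** The design has two randomisations. Under Study design, "The study is being implemented in eight sites in Manicaland Province, east Zimbabwe", and "In each site, two matched clusters of villages will be created". One cluster of each pair goes to intervention and one to control, giving eight of each. The second step is at the level of the man: "Within the intervention clusters, individuals will be further randomly assigned to receive one of two incentives". Randomisation/masking adds: "Blocks of four will be computer-generated and allocated to one of the two treatment arms in a 1:1 ratio".

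The Statistical analysis section gives a single model for each endpoint: "a linear regression will be used to estimate differences in the cluster-level prevalence of the indicator at follow-up". The only covariates it mentions are indicators found unbalanced at baseline. If the residuals fail a Shapiro–Wilk test, it turns to non-parametric tests and offers the Mann–Whitney rank-sum test as the example. It names no cluster, pair or site term, and it does not rule one out. It gives no separate analysis for fixed against lottery.

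Interest in that contrast is visible elsewhere. The Background argues that a lottery may have more effect than a fixed sum, and the Discussion says: "Findings from the study will help determine which type of financial incentive is an effective tool to create demand for VMMC".

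**The concern.** A cluster-level regression suits intervention against control, because clusters are what was randomised there. It does not suit fixed against lottery, where each intervention cluster contains both arms. Two literal readings are possible.

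- **One prevalence per cluster.** There are 16 rows, and no row belongs to fixed or to lottery alone. The contrast cannot be estimated.
- **One prevalence per cluster and arm.** The contrast can be estimated, but the two rows from a cluster share that cluster's effect. Without a cluster or pair term, an ordinary regression or rank-sum test treats them as independent. Variation between clusters, which cancels in the difference, then stays in the error term.

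At stake is the precision of the incentive comparison. On the second reading its confidence interval would be too wide, and a moderate real difference could well be reported as none.

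**Working it through.** **Inputs from the protocol article.** Eight intervention clusters (Study design). "It is estimated that a sample size of 580 participants per arm will be necessary to detect meaningful minimum effect sizes", and "A total of 1740 males will be enrolled". From Sample size estimates: intra-cluster correlation ρ = 0.04, taken from HIV incidence; reference rate 30%; 80% retention at 6 months. Significance level 0.05, taken as two-sided.

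**The plan's own figure.** 3 × 580 = 1740, so the total is consistent. The 580 cannot be reproduced, because neither a target effect nor a power is stated.

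**Men per cluster and arm.** 580 / 8 = 72.5 enrolled; 580 × 0.8 = 464 followed up, and 464 / 8 = m = 58.

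**Variance of fixed minus lottery, p = 0.30.**

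- No cluster or pair term: 2p(1−p)[ρ + (1−ρ)/m]/8 = 0.42 × (0.04 + 0.01655)/8 = 0.00297, so SE = 0.0545.
- Within clusters: 2p(1−p)[(1−ρ)/m]/8 = 0.42 × 0.01655/8 = 0.00087, so SE = 0.0295.
- Variance ratio: (0.04 + 0.96/58)/(0.96/58) = 3.42, so the SE ratio is 1.85.
- With all 580 per arm (m = 72.5): 0.0529 against 0.0264, ratio 2.0.

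**Sensitivity to ρ at m = 58.** The SE ratio is 1.26 at ρ = 0.01, 1.48 at 0.02, 1.85 at 0.04 and 2.46 at 0.08. The number of clusters cancels from the ratio.

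**Power at 464 per arm, ρ = 0.04, from 30%.** The effect sizes are assumptions. The normal approximation for the unpaired column divides 464 by the design effect 1 + 57 × 0.04 = 3.28. Simulations used 20,000 runs per setting.

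| Difference (points) | Individual-level, normal approx. | Unpaired, normal approx. | Unpaired t on 16 cluster-arm rows, simulated | Paired cluster-level t, simulated | Cluster-stratified individual-level, simulated |
|---|---|---|---|---|---|
| 5 | 37% | 14% | 5% | 30% | 39% |
| 7.4 | 67% | 26% | 14% | 55% | 69% |
| 10 | 89% | 42% | 33% | 79% | 90% |
| 12 | 97% | 56% | 52% | 91% | 97% |
| 15 | 99.7% | 74% | 76% | 98% | 99.8% |

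The simulated unpaired figures differ from the approximation for a reason. The estimate really varies with a standard deviation of about 0.031, while the test divides it by an SE of about 0.0555. At 10 points the typical statistic is 0.10/0.0555 = 1.80, below the critical value of 2.14 on 14 degrees of freedom. At 15 points it is 0.15/0.0561 = 2.67, above it.

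**Type I error.** With no true difference, the unpaired t-test on 16 rows rejects in about 0.2% of runs against a nominal 5%. A regression over all three arms without a cluster term rejects in about 0.1%. The paired and stratified tests reject in about 5%.

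**Where the loss comes from.** At 10 points the paired cluster-level analysis has a mean SE of 0.030, against 0.031 for the individual-level analysis. Its power of 79% rather than 90% reflects having only 7 degrees of freedom.

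**The case against.** The strongest reply is that the unpaired model is inferred. The article calls the design matched, describes a linear regression without listing all its terms, and condenses a fuller protocol that may include cluster or pair indicators. The Mann–Whitney test is only an example and applies only if residuals look non-normal. This stands in part: the size of the problem must be stated conditionally. It does not remove the point, because the article does fix one model for every endpoint, and on either literal reading that model does not fit this contrast.

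Further objections carry weight:

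- A reader might infer that working with cluster-level prevalences itself nearly doubles the SE. The calculations do not support that. Paired differences of the same prevalences keep almost all the precision; the missing cluster or pair term does the damage.
- Fixed versus lottery is not a declared primary comparison. The Abstract sets the two incentives against control, the study hypothesis concerns the package with either incentive, and the Discussion sentence could mean each type against control.
- The effect sizes are assumed, and the correlation comes from HIV incidence rather than circumcision uptake. At ρ = 0.01 the inflation is modest.
- Sample size estimates has the two community-conversation pairs examined separately, so the main analysis may use six pairs. At the same m the SE ratio is unchanged, but every power figure would be lower.
- The error is conservative and the trial is a pilot. There is no bias and no excess of false positives.

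**Conclusion.** The mismatch holds, and its size is conditional. If rows are formed by cluster and arm and no cluster or pair term is fitted, the SE for fixed versus lottery is about 1.85 times too large at 464 per arm and ρ = 0.04, and about 2.0 times at 580. Power is roughly halved for an assumed difference near 10 points and proportionately less reduced at 15. These figures assume equal cluster sizes, a cluster effect common to both arms and no variation of the incentive difference between clusters.

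A reader might go further and conclude that the plan's intervals for this contrast are certainly too wide, or that any real difference would be missed. The document supports neither: it does not exclude a cluster term, and a 15-point difference would still be detected about three times in four. The contrasts with control are not affected by this argument. The point should be fixed, but it does not threaten the trial's validity.

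**What to change.** Add to Statistical analysis that fixed versus lottery is estimated on individual data from men in the intervention clusters only, by randomised arm, with cluster as a fixed stratum: a regression with cluster indicators, or a Mantel–Haenszel risk difference. An acceptable alternative is the within-cluster difference in prevalence analysed as paired data, with a paired non-parametric fallback such as the Wilcoxon signed-rank test. Keep the cluster-level regression for the contrasts with control, and do not enter the two arms of one cluster as independent rows.

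If a stratified or paired model is already intended, the same sentence should say so and replace the unpaired fallback for this contrast. The cost is a sentence or two; no data, visits or participants are added.

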### Study setting

The study is being conducted in the Manicaland province (in east Zimbabwe), which covers an area of 36,459 km^2^ (14,077 square miles) and has a population of about 1.75 million (2012). Six sites enumerated in a general population cohort survey that ran from 1998 to 2013 [19] – two small towns, two large agricultural estates and two rural villages – will be included in the study, together with two new sites in a high-density urban suburb in Mutare, the provincial capital. The total estimated population size in these areas is 35,760 people. Data available from previous surveys in six study sites included in the current study show that, in 2012–13, HIV prevalences were 13.5% for males aged 15–54 years and 18.8% for females aged 15–54 years.

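### Clusters are randomised in matched pairs, but the only fallback test named is unpaired and the stated covariate rule does not keep the pairs; if matching works, the test is conservative and precision is lost

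*Protocol article*

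**What the plan says.** The protocol article describes a pair-matched allocation. Study design: "The study is being implemented in eight sites in Manicaland Province, east Zimbabwe". After Fig. 1: "In each site, two matched clusters of villages will be created", then "Clusters will be randomly allocated to the intervention arm or to the control arm". Randomisation/masking says that "two matched clusters of villages will be created on the basis of socio-economic characteristics" and adds distances to trading centres, major roads and health centres as matching factors. Sample size estimates uses the language of pairs for the community conversations: "It will take place in only two cluster pairs". Study setting shows how different the sites are: "two small towns, two large agricultural estates and two rural villages", plus two new sites in a high-density urban suburb.

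For the analysis, the Statistical analysis section says that "a linear regression will be used to estimate differences in the cluster-level prevalence of the indicator at follow-up". Indicators found unbalanced at baseline become covariates. A Shapiro–Wilk test is applied to the model residuals, and "standard non-parametric tests (e.g. Mann–Whitney rank-sum test) will be used in case of non-normality". Effect sizes are to carry 95% confidence intervals, with significance at 0.05. The section does not mention the pair or the site.

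**The concern.** When clusters are matched and one of each pair goes to each side, the two cluster prevalences in a site tend to move together. An analysis that treats the 16 clusters as independent leaves the differences between sites in the error term. The standard error of the intervention–control difference is then overstated, the test rejects too rarely, and the interval can be wider than the design allows.

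Two statements in the text point that way. First, the only stated rule for entering covariates is baseline imbalance. Matching tends to balance the matching factors, so that rule would not normally bring them in. Second, the one fallback test named is unpaired and cannot carry the covariates that the regression would have.

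With eight pairs, or six without community conversations, the trial has little precision to spare. The Background cites earlier increases in uptake of 7.4% and 7.6%. The stated design inputs support detection of a difference roughly twice as large (see the working).

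**Working it through.** **The plan's own figure.** The 580 per arm cannot be reproduced, because the article gives neither the target difference nor the power. With its 30% rate, ICC of 0.04 and 80% follow-up, each cluster contributes 580/8 × 0.8 = 58 per arm. The design effect is 1 + 57 × 0.04 = 3.28, so the effective size is 464/3.28 = 141 per arm. At two-sided 5% and 80% power that detects about 16 points (16.3 with the stated cluster-size CV of 0.17). I therefore use +15 points as an illustration.

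**Inputs.** From Sample size estimates: control rate 30%, ICC 0.04 (given for HIV incidence, applied here to uptake), 80% follow-up. From Study design and Sample size estimates: 8 pairs, or 6 without the community-conversation pairs. Assumed: two-sided test, equal cluster sizes, normal cluster effects, one incentive arm compared with control. The documents do not give the share *s* of between-cluster variance explained by site, so it is varied.

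**Interval width.**
- Variance of a cluster prevalence: p(1−p)[ICC + (1−ICC)/m] = 0.21 × (0.04 + 0.96/58) = 0.21 × 0.0566 = 0.0119.
- Within-pair correlation: r = s × 0.04/0.0566 = 0.707 s, so r cannot exceed about 0.71.
- Unpaired half-width, K pairs: t(2K−2) × √(2 × 0.0119/K). For K = 8: 2.145 × 0.0545 = 11.7 points, whatever r is.
- Paired half-width: t(K−1) × √(2 × 0.0119 × (1−r)/K). For K = 8: 2.365 × 0.0545 × √(1−r).
 - s = 0: 12.9 points, so the unpaired interval is 9% narrower.
 - s = 0.5 (r = 0.354): 2.365 × 0.0545 × 0.804 = 10.4 points, so the unpaired interval is about 13% wider.
- Break-even: r = 1 − [t(2K−2)/t(K−1)]².
 - Eight pairs: 1 − (2.145/2.365)² = 0.18, so s = 0.18/0.707 ≈ 0.25.
 - Six pairs: 1 − (2.228/2.571)² = 0.25, so s = 0.25/0.707 ≈ 0.35.

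**Simulation** (58 per cluster, 10,000 runs for the t tests, 3,000 for the rank tests; power is for 30% v 45%):

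| Pairs | Site share | Type I: unpaired t / Mann–Whitney / paired t | Power: unpaired t / Mann–Whitney / paired t / signed-rank |
|---|---|---|---|
| 8 | 0 | 4.7 / 3.7 / 5.0% | 71 / 68 / 65 / 57% |
| 8 | 0.25 | 3.2 / 3.3 / 4.9% | 73 / 67 / 73 / 65% |
| 8 | 0.50 | 2.0 / 1.8 / 5.5% | 75 / 71 / 82 / 76% |
| 8 | 0.75 | 0.9 / 0.7 / 4.6% | 77 / 74 / 91 / 86% |
| 6 | 0 | 5.0 / 4.6 / 5.1% | 56 / 50 / 47 / 32% |
| 6 | 0.50 | 2.1 / 1.6 / 4.8% | 56 / 51 / 63 / 44% |

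Repeated simulations of the setting with eight pairs and a 50% share gave 74–75% unpaired and 81–82% paired. Mann–Whitney ranged from 64% to 71%; using or omitting the continuity correction alone moved it between 68% and 71%.

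**The pre-test.** With eight pairs, Shapiro–Wilk triggered the switch in about 4–7% of runs. With no site effect the two-stage type I error was 4.2%, against 4.7% for the t test alone. At a 50% share the two-stage power was 75%, the same as for the t test.

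**The case against.** The strongest reply is that the article is condensed and its analysis plan is not shown. A linear regression on cluster prevalence does not exclude a site term, and Mann–Whitney is only an example of the standard tests. This stands in part. A reader might infer that the regression certainly omits the pairs, and the text does not establish that. It does state a covariate rule that leaves them out and a fallback that is unpaired.

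A reader might also infer that the intervals are too wide in any case. The documents give no within-pair correlation. Below the break-even the unpaired interval is the narrower one, and with so few pairs, giving up the matching to keep 14 rather than 7 degrees of freedom is a defensible choice if made in advance. The range of site types makes effective matching plausible but does not show it.

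Three further readings are not supported:
- The normality test does not distort error rates; the working shows almost no effect under normal cluster effects. For the same reason the Mann–Whitney figures are the cost when the fallback is used, not the average cost of the plan.
- The rank-sum test does not rule out an interval. It can be inverted to give one for a shift in cluster prevalence, although without covariate adjustment.
- Nothing here suggests false positive results.

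**Conclusion.** The point holds as a mismatch between a pair-matched allocation and an analysis description whose one named fallback is unpaired and whose covariate rule does not retain the pairs. For any positive within-pair correlation, an analysis that ignores the pairs is conservative: about 3% true type I error at a 25% site share, 2% at 50% and 1% at 75%.

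Precision and power are lost only when matching is effective. That means a site share above about 25–30% with eight pairs and about 30–35% with six. At a 50% share the loss is about 7 points of power against the paired t test, and 11–17 points when Mann–Whitney is used.

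These sizes rest on the ICC for HIV incidence applied to circumcision uptake, 58 analysed per cluster in each arm compared, and an illustrative 15-point effect. They concern intervention against control; fixed cash against lottery is randomised to individuals within clusters and is a separate comparison. The point is worth correcting because the change is cheap, but it does not threaten the validity of a positive finding.

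**What to change.** State that intervention v control is analysed as within-site differences, by site fixed effects in the cluster-level regression or equivalently a paired t test. That gives 7 degrees of freedom with all eight pairs, or 5 if the two community-conversation pairs are analysed separately; the text should say which applies. If the team prefers to drop the matching to save degrees of freedom, it should say so in advance and give the reason.

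Remove the normality-triggered move to Mann–Whitney. Name one robustness check that is always reported: a within-pair permutation test (2⁸ = 256 allocations for eight pairs, 2⁶ = 64 for six) or the signed-rank test. Keep it as a check and not as the primary test. Its smallest two-sided p-value is 2/256 = 0.008 with eight pairs and 2/64 = 0.031 with six, and with six pairs signed-rank power was only 44% at a 50% site share. With two pairs the minimum is 2/4 = 0.5 (Mann–Whitney 0.33), so neither can reach 0.05 for the community-conversation sites alone.

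The cost is wording plus fewer degrees of freedom. If matching proves uninformative, the paired t test loses about 6 points of power with eight pairs (71% to 65%) and about 9 with six (56% to 47%). No change to conduct or data collection is needed.
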